### Adverse Reactions

All adverse reactions will be recorded. In the published literature on NET there have been no documented adverse reactions [13,15-20]. It is not anticipated that participants will be exposed to any unnecessary risks. Due to the nature of the NET procedure/study protocol there is potential for a mild uncomfortable recall of past events in the NET treatment group. There is also potential for some mild focal soreness following the tapping procedures applied in both the NET and the placebo groups. Any participant experiencing anything more than a mild discomfort/soreness, or becoming emotionally distressed, will have their participation in the study reviewed and their potential for withdrawal assessed. In the case of any adverse reaction, the relevant help will be rendered to the participant at no charge. The primary health care provider will also be notified in the event of any significant changes/revelations in a participant's health status that are witnessed prior to commencement or during a participant's involvement in the trial.

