It is anticipated that the majority of participants will be receiving treatment in the form of L-Thyroxine supplementation. For this reason, serum measures of TSH, serum FT4, serum FT3 should fall within normal reference ranges (See Table 1) provided there are no major alterations to this existing treatment strategy. In adequately treated participants, the addition of the experimental intervention should not influence serum thyroid hormone levels. However, in individuals who are not being medicated, or in individuals who are being under-treated upon entry into the trial, a decrease in TSH measurements and an increase in FT4 and FT3 measurements may be expected during the course of the trial.

In individuals who are being over-treated, elevated FT4 and FT3 levels and decreased TSH measurements will be demonstrated at baseline. It is expected that there will be no change in the serum measures in this subgroup.

It is unclear how the autoimmune markers will respond to the addition of NET to any existing treatment regimens.

In addition to the serum measures, participants will fill out the SF-36v2 and the additional items (anxiety and stress) of the DASS.

The SF-36v2 health survey is a questionnaire used to assess outcomes in eight different domains: role limitations because of physical or emotional problems, physical and social functioning, bodily pain, perception of mental and general health, and vitality [34].

Improvements in functional health and well-being as measured by the SF-36v2 will be depicted by increased scores by the respondents at six weeks and at six months. Deterioration in functional health and well-being will be revealed by a decrease in SF-36v2 scores.

Two additional secondary outcome measures are to be completed and recorded by participants at home for each day of the six month trial period are listed below:

Basal Heart Rate (BHR)

Basal Temperature (BT)

After signing up to take part in the trial, participants will be given a home diary, digital thermometer and instructions on how to record their BHR and BT. Participants will be instructed to make an effort to perform these measurements at the same time each day, and ideally before getting out of bed in the morning. For BHR measurements, participants will be instructed to find their radial pulse and then record the number of beats that occur in one minute and record this figure in the diary provided.

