### Power analysis and sample size justification

A (one-sided) power analysis indicated 51 subjects per group will yield an 80% chance of detecting a decrease in depression scores of at least four points in treatment compared to control using a standard deviation of eight based on simulation. Clinically, a four point reduction in depression scores, as defined by the DASS, would represent a meaningful reduction in depressive states. A four point decrease may indicate that an individual has gone from expressing moderate to mild states of depression or mild to normal expression of depressive states [32].

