### Statistical Analysis

Two-sample t-tests will be used to compare change from baseline for NET treatment versus control at each of six weeks and six months for the primary outcome measure. Linear mixed-effects models will be used examine change over time in the treatment and placebo groups for the basal temperature and basal heart rate groups as well as the other secondary outcome measures. A significance level of 5% will be used throughout the analysis. Because the analyses will be seen as hypothesis generating, no adjustment for multiple testing will be used. The R software program [39] will be used to conduct the analyses. Complete case analysis will be employed for participants who strictly followed the trial protocol. Sensitivity analysis will be used for withdrawals, missing data and participants who violate the study protocol eg. changes in medication during the study period. This will be done using imputation techniques including last value carried forward, and multiple imputation.

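### The only analysis not labelled a sensitivity analysis is restricted to complete cases who strictly followed the protocol, so the primary comparison is not made as randomised

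*Protocol article*

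**What the plan says.** The primary outcome is DASS depression, measured at baseline, six weeks and six months. The test is given in Statistical Analysis: "Two-sample t-tests will be used to compare change from baseline for NET treatment versus control at each of six weeks and six months". The same section then fixes who is analysed: "Complete case analysis will be employed for participants who strictly followed the trial protocol". Everyone else is placed elsewhere: "Sensitivity analysis will be used for withdrawals, missing data and participants who violate the study protocol eg. changes in medication during the study period". The method follows: "This will be done using imputation techniques including last value carried forward, and multiple imputation".

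Other sections bear on who would be excluded:

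- **Informed Consent, Inclusion Criteria, and Withdrawals and Protocol Violations.** Participants are not asked to alter existing treatment. Changes in treatment or medication during the trial are to be recorded, and the last of these sections says they will be taken into account in the final analysis and interpretation. None of the three prohibits a change or defines an analysis set.
- **Adverse Reactions.** One risk is named for a single arm: "there is potential for a mild uncomfortable recall of past events in the NET treatment group". Mild soreness from tapping is foreseen in both arms. A participant whose discomfort is more than mild, or who becomes emotionally distressed, is reviewed for possible withdrawal.
- **Blinding.** The treating practitioners know the allocation.
- **Methods (objectives) and Discussion.** The question is what NET does when added to whatever management the participant already has.

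**The concern.** Randomisation makes the arms comparable at the moment of allocation. Staying complete and strictly adherent for six months is decided afterwards. If the reasons for dropping out of that set differ by arm and relate to depression, the remaining groups are no longer comparable, and the t-test on change from baseline mixes the treatment effect with selection.

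The question answered also shifts. A pragmatic add-on question covers people whose other management changes during follow-up. The stated set removes them, although elsewhere the article treats such changes as ordinary events to be written down. What is at stake is the primary estimate of the trial at both six weeks and six months.

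**Working it through.** **1. Is this the main analysis set?** The article does not use the word primary for it. However, participants outside the strict complete-case set appear only under sensitivity analysis, and a sensitivity analysis needs a reference analysis. The strict complete-case set is the only candidate. This is an inference, but a firm one.

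**2. Can exclusion depend on arm?** Set side by side: uncomfortable recall is named for the NET arm only; emotional distress leads to a review for withdrawal; the practitioners know the allocation; and a medication change counts as a violation. Distress lies close to the primary outcome. Removal that differs by arm and is related to outcome is therefore possible. The article gives no rates, so it cannot be shown to occur.

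**3. The plan's own figure.** Inputs from the sample size section ("A (one-sided) power analysis indicated 51 subjects per group will yield an 80% chance"): difference 4, SD 8, one-sided, with the 5% level from Statistical Analysis ("A significance level of 5% will be used throughout the analysis").

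- Normal approximation: n = 2 × (1.645 + 0.842)² × 8² / 4² ≈ 49.5, so 50 per arm.
- Exact t-test: 51 per arm, power 80.6%. The stated 51 is reproduced.

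There is no allowance for exclusions. With assumed losses, one-sided power is 76.1% at 45 per arm (about 10% lost) and 71.6% at 40 per arm (about 20%).

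**4. Illustration of bias.** Assume no true effect and SD 8. In each arm a fraction f with the highest exclusion propensity is removed, and that propensity has correlation ρ with a worse change score. The mean of those who remain shifts by −8 × ρ × φ(z)/(1 − f), where z is the upper-f point of the standard normal and φ is its density. The bias is the difference between arms.

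- f = 15%: φ(1.036)/0.85 = 0.2332/0.85 = 0.274
- f = 5%: φ(1.645)/0.95 = 0.1031/0.95 = 0.109
- Difference 0.166; times 8 = 1.33; times ρ = 0.3, 0.5, 0.8 gives 0.40, 0.66, 1.06 points
- f = 12% v 8%: 0.2273 − 0.1616 = 0.0657; times 8 = 0.53; times ρ = 0.3 to 0.8 gives 0.16 to 0.42 points
- f = 10% v 10%, same mechanism: zero

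Simulation at 51 per arm for 15% v 5%, with more removed from NET:

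| ρ | spurious benefit (points) | one-sided error in favour of NET | two-sided error |
|---|---|---|---|
| 0.3 | 0.38 | 7.9% | 6.0% |
| 0.5 | 0.66 | 10.8% | 6.9% |
| 0.8 | 1.08 | 17.4% | 10.6% |

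Both error columns are given because the sample size is one-sided while the analysis section does not state sidedness. Reversing either the arm with more removals or the sign of ρ gives the same sizes against NET.

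Equal rates alone do not protect. With 10% removed from each arm, at random under placebo but with ρ = 0.3 to 0.5 under NET, the shift is about 0.5 to 0.8 points.

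**5. Last value carried forward.** There are three DASS time points. If no follow-up score exists, the baseline is carried and the change is zero. If only the six-month score is missing, the six-week score is copied, which presumes the durability that the six-month objective is meant to test.

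**The case against.** The strongest case on the other side has five parts.

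- **The trial is a pilot, its analyses are called hypothesis generating, and multiple imputation is already planned.** This limits the consequence. It does not justify the analysis set: the hypothesis-generating label is used only to waive multiplicity adjustment, and the trial is sized for a between-group test.
- **A reader might infer that distressing recall is foreseen in the NET arm and leads to removal.** The article does not say so. It foresees mild recall, which lies below its own threshold for review; soreness, another possible trigger, is foreseen in both arms; and review is not removal. What stands is that the path from recall to distress is more open in one arm.
- **A reader might infer that bias would favour NET.** The documents do not support that. For hormones they anticipate "in individuals who are not being medicated, or in individuals who are being under-treated upon entry into the trial, a decrease in TSH measurements", with FT4 and FT3 rising. If such an improvement prompted a medication change, the participants removed could be apparent responders, which would bias against NET. Persistent under-treatment might equally prompt changes under placebo.
- **A reader might infer that the sensitivity analysis makes matters worse.** It cannot alter the primary estimate, and bringing the excluded participants back in lessens the problem. The text can be read as imputing over scores that violators did provide, but it does not say that observed values are discarded.
- **Replacing the t-test is not required.** This is right. The defect is the analysis set; a mixed model is one option for handling missing scores.

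**Conclusion.** The point holds. A stated rule, not a detail left to an analysis plan, makes strict-protocol complete cases the only non-sensitivity analysis set. Exclusion occurs after randomisation, may differ by arm, and removes people whom the add-on question covers.

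Neither the direction nor the size of bias can be read from the article. The removal rates and correlations used here are assumptions. Within them, bias runs from near zero (equal removal by the same mechanism), through about 0.2 to 0.4 points (12% v 8%), to about 0.4 to 1.1 points (15% v 5%), which is roughly 10% to 27% of the 4-point target. In the last case the false-positive rate is about 8% to 17% one-sided, or 6% to 11% two-sided, if the bias favours NET. These figures show what the rule permits. A reader who took them as a forecast, or as evidence of a pro-NET bias, would go beyond the documents.

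**What to change.** Reword Statistical Analysis before any unblinded look at the data:

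- **Primary analysis:** all randomised participants in their allocated arm, using every observed DASS score whatever the adherence or medication change.
- **Missing scores:** use the multiple imputation already planned, or a mixed model such as the one planned for the secondary outcomes, only for scores that are truly missing.
- **Supportive analysis:** the strict-protocol complete-case comparison, labelled as such.
- **Sensitivity:** do not rely on last value carried forward. Add a shift analysis in which missing scores are made progressively worse, including by different amounts in the two arms, because withdrawal linked to distress may violate missing at random.

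The cost is slightly more analysis work and possibly a diluted effect estimate, since participants who adhered poorly are kept. Rewording recovers scores that violators provided. It cannot recover scores from those who withdrew, because the article describes follow-up only to confirm the withdrawal and invite a reason; for them the result rests on the imputation and the shift analysis.

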### Measures

The standard guidelines for the assessment of individuals with thyroid dysfunction will be used by the primary care providers to establish the diagnosis of hypothyroidism [1]. The primary and secondary outcome measures (DASS, SF-36v2 and Serum Measures) will be applied pre-intervention to obtain baseline data, then reapplied at six weeks (post-intervention) and six months (study conclusion). Measurement of basal heart rate and basal temperature will be applied for each day of the six month study period, and will commence one week prior to the research intervention.

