Due to the chronotropic effect of the thyroid hormones on heart rate, untreated or undertreated individuals will demonstrate lower heart rates at baseline. It is anticipated that if NET therapy has a positive influence, there may be a trend over time toward slight increases in heart rate.

Basal temperature recording will be performed using a digital thermometer placed under the axilla. The thermometer will be placed under the axilla for approximately two minutes and the resultant temperature reading recorded.

Due to the thermogenic action of thyroid hormones, it is hypothesised that unmedicated or under-treated participants will experience an increase over time in basal temperature that may approach normal ranges of basal temperature (35.5 - 37.0°C) with the addition of NET treatment [35]. Adequately treated individuals should display normal basal temperatures at baseline that remain unperturbed by any additional treatment.

The secondary measures of basal heart rate and temperature measurement to be employed in this research study are commonly used by thyroid specialists as a crude measure of thyroid performance that is adjunctive to the hormone assays [36-38].

The recording of BHR and BT will begin one week prior to the initial intervention and continue for each day of the clinical trial.

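### The complete-case, strict-adherence rule makes no exception for basal temperature and heart rate, recorded daily for about 189 days, although the planned mixed models could use every recorded day

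*Protocol article*

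**What the plan says.** All the analysis rules are in the protocol article, Statistical Analysis.

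- Model: "Linear mixed-effects models will be used examine change over time in the treatment and placebo groups for the basal temperature and basal heart rate", and for the other secondary outcomes.
- Rule for the main analysis: "Complete case analysis will be employed for participants who strictly followed the trial protocol". No outcome is exempted.
- What happens to the rest: "Sensitivity analysis will be used for withdrawals, missing data and participants who violate the study protocol". The method follows: "This will be done using imputation techniques including last value carried forward, and multiple imputation".

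The recording schedule appears in two other sections. Under Measures: "Measurement of basal heart rate and basal temperature will be applied for each day of the six month study period". Under Secondary Outcome Measures, the readings are to be "completed and recorded by participants at home for each day of the six month trial period", and "The recording of BHR and BT will begin one week prior to the initial intervention and continue for each day of the clinical trial".

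The article does not define a complete case for an outcome measured repeatedly. It does not say whether a missed diary day breaches strict adherence. Its one example of a violation is a change in medication.

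**The concern.** A linear mixed model fitted by likelihood accepts a different number of readings from each person. It gives valid estimates from the recorded days if readings are missing at random. A complete-case rule gives up that advantage, and the cost grows with the number of planned readings: it may be small for a questionnaire given three times, but it can be large for a diary kept every day for half a year.

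Three features of the text favour reading the rule at participant level. It is worded in terms of participants, not readings. Missing data are sent to a separate analysis by imputation, which would not be needed for isolated missed days if the main model already used all the others. Daily recording is also part of the protocol, so a gap could be held to breach strict adherence.

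At stake are the precision of two secondary outcomes and who contributes to them. The article states expected directions of change over time for both. On the participant-level reading, the main estimate of those trends would come from the most diligent diary keepers, while valid readings from everyone else would wait for a sensitivity analysis.

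**Working it through.** **The plan's own figure.** The article gives no figure for diary completeness or for the number expected in the diary models. Its only sample-size figure is 51 per group (Power analysis and sample size justification). For a difference of 4, SD 8, one-sided 5% and 80% power, n = 2 × (1.645 + 0.842)² × 8² / 4² ≈ 49.5, so 50 per group by the normal approximation. The exact t calculation gives 51, with power 80.6%. The figure reproduces. Here it only supplies the total of 102.

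**Planned readings.** Six months is taken as 182 days, plus 7 days before treatment: 182 + 7 = 189 per person per outcome. Over 102 people this is 102 × 189 = 19,278 readings per outcome.

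**Participant-level reading, independent misses.** Let m be the daily miss rate. It is an assumption, because the article gives none. The share with a complete diary is (1 − m)^189, and the expected number is 102 times that.

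**Participant-level reading, clustered misses.** Let each person's miss rate follow a beta distribution with mean m and concentration c, so a = mc, b = (1 − m)c and the intraclass correlation is 1/(1 + c). The share with a complete diary is B(a, b + 189)/B(a, b). Example: m = 2%, c = 20 (correlation about 0.05) gives a = 0.4, b = 19.6, share 0.386, and 102 × 0.386 ≈ 39 people. The ranges below run from c = 20 to c = 1 (correlation about 0.05 to 0.5).

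**All recorded days used.** The readings kept are 19,278 × (1 − m).

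| Missed days (assumed) | (1 − m)^189 | Complete diaries of 102, independent | Complete diaries of 102, clustered | Readings kept of 19,278 if all days are used |
|---|---|---|---|---|
| 0.1% | 0.828 | 84 | not run | 19,259 |
| 0.5% | 0.388 | 40 | not run | 19,182 |
| 1% | 0.150 | 15 | 63 to 96 | 19,085 |
| 2% | 0.022 | 2 | 39 to 91 | 18,892 |
| 5% | 0.00006 | 0 | 9 to 76 | 18,314 |
| 10% | about 0 | 0 | 1 to 57 | 17,350 |

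**Row-level reading.** If complete case means only that rows with a missing value are dropped, one missed day costs one reading and no participant is lost for it. The restriction to strict adherence still applies. Someone who withdraws at the end of the six treatment weeks may have 7 + 42 = 49 recorded days, and someone whose medication changes may have all 189. On the stated rule, neither set of readings enters the main analysis. The total loss cannot be computed, because the article gives no expected rate of withdrawal or violation.

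**The case against.** The strongest reply is that the plan nowhere says one missed day excludes a participant. In a data set with one row per reading, complete-case analysis can mean dropping empty rows, and naming a mixed model for these outcomes fits that reading. This stands: exclusion for a single missed day is something a reader might infer, not something the article states.

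A reader might also infer that almost nobody would be left. The article does not support that either. It gives no miss rate and nothing on how misses are distributed, and independent days are implausible when some people keep diaries far better than others. With clustering, most or many participants can remain.

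It can also be said that the definition belongs in a fuller document, that only two secondary outcomes of a hypothesis-generating pilot are affected, and that participants with missing data return through multiple imputation. The limited stakes are granted. But the article does more than leave a term undefined. It states a rule, exempts no outcome, and confines the main analysis to strict adherers. On either reading, recorded days from withdrawn and non-adherent participants reach the results only through an imputation-based sensitivity analysis.

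Finally, imputation could be barred for these outcomes altogether. That would be a preference: nothing in the article shows multiple imputation to be wrong as a sensitivity analysis.

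**Conclusion.** The point holds in a limited form. A complete-case rule restricted to strict adherers covers every outcome, including two with about 189 planned daily readings, and fits poorly with the mixed models chosen for them.

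The size depends on the reading and on unstated rates. At participant level the loss runs from modest (84 of 102 kept at 0.1% independent misses) to nearly total (2 of 102 at 2%), and is much smaller if misses cluster (39 to 91 at a mean of 2%). At row level it is confined to readings from withdrawn or non-adherent participants, in a number the article does not allow one to estimate. The miss rates, the clustering and the 182-day half-year are assumptions.

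The consequence is avoidable loss of data and possible selection in two secondary, exploratory outcomes. The change should be made because it removes the ambiguity on either reading at almost no cost.

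**What to change.** In Statistical Analysis, add a sentence stating that the main mixed models for basal temperature and basal heart rate are fitted by likelihood to every recorded day of every randomised participant, without requiring a complete diary. The complete-case analysis of strict adherers and multiple imputation may stay as sensitivity analyses for these outcomes.

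The cost is one sentence. No new data are needed, and the main analysis takes less work than imputing daily values. The downside should be stated with it: the main diary analysis then relies on readings being missing at random given the data in the model, and it includes participants who did not adhere, so it no longer describes strict adherers alone. The retained sensitivity analyses show how far the result depends on either.

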## Methods

The objectives of this research are described below:

1) To determine whether the addition of NET to concurrent management regimens can improve clinical outcomes in a sample of individuals with primary overt hypothyroidism. For Example, reducing the severity of depression scores at six weeks and six months; 2) To determine the short and medium term responses to NET via changes to the primary and secondary outcomes in this sample.

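### Last value carried forward is a poor sensitivity method for the two DASS depression contrasts: it can bias them in either direction and merges the six-week and six-month responses

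*Protocol article*

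**What the plan says.** All references are to the protocol article.

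- **Main analysis (Statistical Analysis):** "Complete case analysis will be employed for participants who strictly followed the trial protocol".
- **Primary contrast (same section):** "Two-sample t-tests will be used to compare change from baseline for NET treatment versus control at each of six weeks and six months", for the DASS depression score.
- **Sensitivity analysis (same section):** "Sensitivity analysis will be used for withdrawals, missing data and participants who violate the study protocol eg. changes in medication during the study period". The method follows in the next sentence: "This will be done using imputation techniques including last value carried forward, and multiple imputation". No outcome or visit is excepted, and neither technique is ranked above the other.
- **Visits (Measures):** DASS, SF-36v2 and the serum measures "will be applied pre-intervention to obtain baseline data, then reapplied at six weeks (post-intervention) and six months (study conclusion"). There is no assessment in between.
- **Objective 2 (Methods):** "To determine the short and medium term responses to NET via changes to the primary and secondary outcomes in this sample".
- **Diary outcomes (Measures; Statistical Analysis):** basal heart rate and basal temperature are recorded daily. They and the other secondary outcomes are assigned to mixed models: "Linear mixed-effects models will be used examine change over time in the treatment and placebo groups".

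**The concern.** Last value carried forward assumes that a participant's score stays where it was last seen. With three visits and a change-from-baseline contrast, that leaves two possibilities. A participant lost before week six has only a baseline score, so the change is 0 at both later visits whatever actually happened. A participant lost between week six and month six has the short-term score counted as the medium-term score, which merges the two responses that objective 2 sets out to distinguish.

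The stakes are higher than the label of sensitivity analysis suggests. The main analysis leaves out everyone with incomplete data or a protocol violation. The imputation analysis is the only one stated that brings those randomised participants back, so it is where a reader will look to see whether the result depends on the exclusions. If one of its two named methods carries a built-in bias of unknown sign, agreement with the main result reassures less than it appears to.

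**Working it through.** **Inputs from the protocol (Power analysis and sample size justification; Statistical Analysis).** 51 per group; difference 4 points; SD 8; one-sided power analysis at 80%; significance level 5%.

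**Inputs assumed, because the protocol gives none.** Loss of 10, 20 or 30%, unrelated to the scores; the SD of 8 applied to change scores; the mean changes stated in each step.

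**1. The plan's own figure.** The normal-approximation sample size is n = 2 × 8² × (1.645 + 0.842)² / 4² = 49.5, so 50 per group. The t-test at 51 per group has 80.6% one-sided power. The stated 51 is reproduced and is not affected by this point.

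**2. Loss between week six and month six.** If a fraction d is lost in each arm, the carried-forward six-month difference is

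(1 − d) × (six-month difference) + d × (six-week difference).

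Take −4 at six weeks and 0 at six months. The standard error is √[(64 + 64 + 16·d(1 − d)) / 51], because the NET arm is a mixture of participants with mean 0 and mean −4. The error rate is P(Z > 1.645 − |difference|/SE).

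| Loss d | False six-month difference | SE | Ratio | One-sided 5% error | Two-sided 5% error |
|---|---|---|---|---|---|
| 10% | −0.4 | 1.593 | 0.25 | 8% | 6% |
| 20% | −0.8 | 1.600 | 0.50 | 13% | 8% |
| 30% | −1.2 | 1.605 | 0.75 | 18% | 12% |

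Simulated t-tests agree to within about half a percentage point (one-sided 8.1/12.2/18.3%, two-sided 5.9/7.7/11.2%). When loss is unrelated to the scores, the correlation between the two change scores does not enter the formula.

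If instead the effect emerges late (0 at six weeks, −4 at six months), the same formula gives −3.6/−3.2/−2.8, so a real effect is diluted.

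**3. Equal loss before week six.** Leavers get a change of 0, so the difference is (1 − d) × (−4) = −3.6/−3.2/−2.8 for d = 10/20/30%. Simulated one-sided power at 51 per group falls to about 77/72/67%.

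**4. Unequal loss before week six, no true effect.** If both arms improve by m points, the spurious difference is (difference in loss rates) × m. With 10% against 25% lost and m = 3 to 5, this is 0.15 × 3 = 0.45 to 0.15 × 5 = 0.75 points. With 10% against 30% and m = 4, it is 0.20 × 4 = 0.8 points. The arm with less loss looks better, so the sign depends on which arm loses more.

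Steps 2 to 4 give bias away from zero, bias towards zero, and bias of either sign. The method cannot be defended as conservative.

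**The case against.** The strongest reply is that last value carried forward is only one of at least two sensitivity methods. Multiple imputation stands beside it in the same sentence, the complete-case analysis is the main one, and the trial is a pilot whose analyses the protocol treats as hypothesis generating. The loss rates and trajectories above are assumptions, and at 10% loss the two-sided error is 6% against a nominal 5%. All of this is true and limits the weight of the point. It does not remove it: the method is named without limit, its effect on a three-visit change score follows by arithmetic, and nothing says which method is followed if the two disagree.

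Three stronger readings are tempting and are not supported.

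- **That observed scores of protocol violators are overwritten.** The sensitivity analysis does cover participants who change medication, and their six-month scores may well exist. But the text never says that an observed score is set to missing or replaced, and carrying forward ordinarily fills only gaps. The handling is left open.
- **That one diary reading is copied for months.** Nothing assigns the method to the daily series. Those outcomes have mixed models, which use incomplete series without imputation. Any inflated diary error rate would also rest on an assumed random-intercept structure that the article does not specify.
- **That the robustness analysis as a whole gives wrong values.** This overlooks the multiple imputation named alongside.

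**Conclusion.** The point holds for the two DASS contrasts. As planned, last value carried forward fixes change at 0 for anyone lost before week six and passes off the six-week score as the six-month score for anyone lost later. Under the assumed 10 to 30% loss, this produces a false six-month difference of 0.4 to 1.2 points when a six-week effect has faded. It removes 0.4 to 1.2 points from a true 4-point difference when loss is early and equal. When early loss is 10% against 25% and both arms improve by 3 to 5 points, it creates a difference of 0.45 to 0.75 points.

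The mechanism follows from the visit schedule and needs no assumption about rates; the size does depend on loss and trajectories that the protocol does not give. The method should be changed, but it is a sensitivity method in a pilot, and the planned sample size and main analysis are untouched by it.

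**What to change.** In Statistical Analysis, delete last value carried forward and keep the multiple imputation already named. For missing DASS scores, run it by arm with baseline and six-week DASS in the imputation model. Add a sentence stating that imputation fills only missing scores, so that observed scores of participants who change medication or otherwise depart from the protocol are kept as observed. State also that the diary mixed models use observed days only. A delta-adjusted version, which makes imputed scores worse by a fixed amount, is an optional addition.

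The cost is a sentence or two of text, slightly more analysis work and possibly wider intervals. No visit, outcome or sample-size figure changes.
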